### Residential center

Evaluation of the PW+ intervention will occur at the only acute residential community SUD treatment program in Rhode Island. The facility contains 16 beds and is located about 20 min outside the state capital in a suburban area. It recently affiliated with the local hospital, but continues to operate as an independent community-based program. Average length of stay is 6–10 days. About five adolescents are admitted per week on average, which equates to approximately 260 admissions per year. Based on past year census data, about 30% of adolescents at the residential treatment center are racial/ethnic minorities, with Hispanic (about 20%) and African-American (about 10%) being the most commonly represented minority groups. There is approximately even representation of male and female adolescents. In the pilot qualitative sample, median household income was $30,000, with an extremely wide range from $18,000 to over $200,000.

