### Assessments

Parents and adolescents will complete a baseline assessment in-person shortly after their admission to residential treatment. Adolescents will be assured of confidentiality and a National Institute of Health Certificate of Confidentiality (CoC) will be obtained, as adolescent self-report use has shown reliability when confidentiality is assured [77–80]. The CoC will allow the research team to refuse to disclose names or other identifying characteristics of research participants in response to legal demands such as subpoena of records. Follow-up assessments will be conducted by an independent evaluator who is blind to condition. During the open trial, there will be follow-up assessment at 6 weeks post-discharge, while during the pilot randomized trial there will be three follow-up assessments at 6, 12, and 24 weeks post-discharge. Follow-up assessments will be scheduled in-person at the residential treatment center; if a parent no-shows more than twice for a follow-up assessment, then research staff will attempt to conduct the follow-up sessions at a location of the family’s choosing (i.e., home, school). The baseline assessment will be 1.5–2 h and the follow-up assessments will be about 1.5 h (see Table 3 for overview of measures).

**Table 3 Tab3:** Overview of protocol measures

Construct	Measurement/scale	Data obtained
Feasibility	Participation rates	Percent of parents who participate in the study
	Parent engagement	Number of coaching sessions attended, online usage of PW and parent message board (i.e., logins, sessions completed, page views, time spent), number of texts viewed
Acceptability	Withdrawal rates	Percent of parents who withdraw from study
	Exit interviews (open trial only)	Open-ended questions on perceptions of in-person sessions, text messages, computer program, and online message board
	CSQ	Satisfaction with treatment delivery and ability to manage their adolescent’s problems
Adolescent substance use	GAIN days of use	Days of alcohol use, marijuana use, and other drug use
	GAIN SFS	Averages percent of past 90 days during which there was use of alcohol, marijuana, or heavy drugs; intoxication; and failure to perform activities due to use
	Gain SUDS	Assesses substance use disorder symptoms in line with both DSM-IV and DSM-V criteria

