	Biological markers	Saliva alcohol screens (12 h window) and 8 panel urine drug screens testing for marijuana, MDMA, cocaine, amphetamines, methamphetamines, opiates, oxycodone, and benzodiazepines
Adolescent high-risk behavior	GAIN risky sex	Series of items about risky sexual behavior over the past 90 days including number of partner, number of sexual contacts, and number of times had unprotected sex
	GAIN days legal	Days of legal involvement over the past 90 days
	GAIN days school	Days of school attendance/truancy over past 90 days
Parenting	PMQ	Parental monitoring and sources of parental monitoring
	PAC	Assesses positive and negative aspects of general parent-teen communication
	FAsTask video code	In vivo problem solving tasks focused on: limit setting; substance use norms; monitoring and listening

*CSQ* customer satisfaction questionnaire, *GAIN* global appraisal of individual needs, *SFS* substance frequency scale, *SUDS* substance use disorder scale, *PMQ* parental monitoring scale, *PAC* parent-adolescent communication scale

We selected adolescent measures to be as consistent with SC as possible. The residential center typically obtains a urine screen and administers a comprehensive adolescent interview to assess substance use and functioning across multiple life domains. We therefore combine biological markers with the Global Appraisal of Individual Needs—Quick (GAIN-Q3 [81]), a well-validated structured interview that assesses adolescents’ problems across several domains: substance use, school, mental health, physical health, risk behaviors, work, and sources of stress. The GAIN-Q3 substance use scales used in this protocol have demonstrated sound psychometric properties including internal consistency [82], high concurrence with the Timeline Followback Method [83], ability to predict SUD diagnoses made by blind raters (κ = .91) [84], and ability to predict substance-related problems as well or better than biometric markers [82]. The PI is a certified trainer of the GAIN family of instruments with experience analyzing GAIN data [85–88] and will train the independent evaluators.

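### Four secondary adolescent measures look back 90 days at a visit 42 days after discharge, so 53% of the 6-week window is pre-discharge time

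*Protocol article*

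**What the plan says.** Table 3 (Assessments) describes the GAIN Substance Frequency Scale (SFS) as follows: "Averages percent of past 90 days during which there was use of alcohol, marijuana, or heavy drugs". Intoxication and role failure due to use also enter that scale. Three further rows carry the same look-back:

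- risky sex: "Series of items about risky sexual behavior over the past 90 days"
- legal: "Days of legal involvement over the past 90 days"
- school: "Days of school attendance/truancy over past 90 days"

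The separate days-of-use row, "Days of alcohol use, marijuana use, and other drug use", states no window.

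For the randomised trial, Assessments says "there will be three follow-up assessments at 6, 12, and 24 weeks post-discharge". At baseline, parents and adolescents "complete a baseline assessment in-person shortly after their admission to residential treatment", and Study enrollment and randomization places allocation during the residential stay. On the length of that stay, Residential center says "Average length of stay is 6–10 days", while Table 2 shows about two weeks.

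Specific aim 2 covers the first 24 weeks after discharge. The section on secondary outcomes plans to compare trajectories over the post-discharge period, with baseline status as a covariate. Nothing in the article shortens the look-back at follow-up.

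**The concern.** The look-back is longer than the time since discharge at the first two visits. The 6-week value is meant to show early change after treatment, yet more than half of its window is time before discharge. Most of that earlier time precedes randomisation, so the intervention cannot have affected it.

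Three planned uses are exposed:

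- **Effect sizes with 95% confidence intervals.** The secondary-outcomes section calls these the main analytical goal, and Sample size and power uses them to judge and size a larger trial.
- **Trajectories and latent growth models.** The three visits measure different mixtures of periods, so part of any apparent change over time comes from the window.
- **Interval-change correlations.** The mediator section correlates change in parenting with change in outcome over each interval. For a 90-day count, the 6-to-12-week change is not change between those two time points.

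**Working it through.** **The plan's own figures.** The article gives no figure for this point. Its only sample-size numbers, 175 per group for d = 0.3 and 64 for d = 0.5 at power 0.8, reproduce with two-sided alpha 0.05 assumed: 175 and 63 by the normal approximation, 176 and 64 by the t-test.

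**Inputs.** Look-back 90 days (Table 3); visits at 6, 12 and 24 weeks, i.e. days 42, 84 and 168 after discharge; stay of 6–10 days (Residential center) or about 14 days (Table 2).

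**Window at each visit.** Pre-discharge days = max(0, 90 − days since discharge).

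| Visit | Window (day 0 = discharge) | Pre-discharge days | Post-discharge share |
|---|---|---|---|
| 6 weeks | −48 to 42 | 90 − 42 = 48 (53%) | 42/90 = 47% |
| 12 weeks | −6 to 84 | 90 − 84 = 6 (7%) | 84/90 = 93% |
| 24 weeks | 78 to 168 | 0 | 100% |

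**Pre-admission days at 6 weeks.** 48 minus the stay: 42, 38 or 34 days for stays of 6, 10 or 14 days, which is 47%, 42% or 38% of the window. All precede randomisation, and all lie inside a 90-day baseline window that ends shortly after admission. Adding an assumed 1–3 days from admission to randomisation gives 35–45 days (39–50%).

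**Overlap between visits.** The 6- and 12-week windows share days −6 to 42, which is 48 days. The 12- and 24-week windows share days 78 to 84, which is 6 days.

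**Dilution.** If the arms differ by a constant amount only after discharge, the observed difference is multiplied by the post-discharge share: 0.47, 0.93 and 1.00, with mean (0.467 + 0.933 + 1)/3 = 0.80. A 10-point difference in percent of days reads as 4.7, 9.3 and 10 points. If the SD is unchanged (an assumption), d = 0.3 averages 0.3 × 0.80 = 0.24. Sizing a trial on the diluted effect then inflates the sample by 1/0.80² = 1.56.

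**Interval change.** For a count, the 12-week value minus the 6-week value is (days −6 to 84) − (days −48 to 42) = (days 43 to 84) − (days −48 to −6). The first 42 post-discharge days cancel. What remains compares weeks 7–12 with a period that is mainly before admission.

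**Illustration (assumed rates).** Take a flat 20% of days used after discharge, none in residence, and a 10-day stay. With pre-admission use p, the 6-week score is (38p + 42 × 0.20)/90.

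| p | 6 weeks | 12 weeks | 24 weeks |
|---|---|---|---|
| 20% | 17.8% | 18.7% | 20% |
| 40% | 26.2% | 18.7% | 20% |
| 60% | 34.7% | 18.7% | 20% |
| 80% | 43.1% | 18.7% | 20% |

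At p = 60%, stays of 6 and 14 days give 37.3% and 32.0% at 6 weeks. A flat post-discharge course shows a spurious fall whose size depends on how heavy pre-admission use was.

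**The case against.** Several points on the other side stand and limit the finding.

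- **No bias between arms.** Pre-randomisation days are balanced in expectation, and any artificial fall appears in both arms. A reader might infer a biased comparison; the documents do not support that. The baseline covariate may also remove some of the noise, but it cannot restore the lost difference.
- **Not mostly pre-treatment.** A reader might infer that the 6-week score is mainly pre-treatment behaviour. By days it is not: pre-admission time is 38–47% of the window. The other pre-discharge days are residential treatment, during which coaching begins. Even if an effect started at admission, the 6-week share would be only (42 + stay)/90, i.e. 53%, 58% or 62% for stays of 6, 10 or 14 days.
- **Not every adolescent outcome.** Days of use and the substance use disorder scale have no stated window, and the saliva alcohol screen covers 12 hours. The point covers four measures.
- **Mainly one visit.** Twelve weeks is slightly affected and 24 weeks not at all. Latent growth models allow for correlation between visits, but they do not undo dilution or a shifting window.
- **Pilot status.** Feasibility and acceptability are the primary outcomes and are untouched, and the article acknowledges unstable effect sizes in small samples.
- **Condensed source.** Table 3 gives one description per instrument, and the full protocol may specify a since-discharge recall at 6 weeks. The article as published fixes 90 days for these measures without distinguishing visits.

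**Conclusion.** The point holds for the SFS, risky sex, legal days and school days. The 53% at 6 weeks follows from the stated window and schedule alone. The 38–47% before admission covers both stated lengths of stay, which disagree with each other without changing the conclusion.

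The harm is dilution and a distorted time course. The factors of 47%, 93% and 100% (about 80% on average, weighting visits equally) assume a constant effect that begins at discharge. They apply to day counts and percentages of days, and only approximately to items such as number of partners. Because the factors rise over the visits, a constant effect can also look like one that grows with time.

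Severity is moderate: the measures are secondary in a 60-dyad pilot, but their effect sizes feed the decision on a larger trial.

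**What to change.** For the count items in these four measures, record days since discharge at 6 weeks and days since the previous scheduled visit date at 12 and 24 weeks. Analyse the percent of days in each interval (about 42, 42 and 84 days). Anchoring on the scheduled date keeps a missed visit from lengthening the next recall period. Keep 90 days at baseline, and ask the standard 90-day items alongside at follow-up if comparability is wanted.

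If only the 90-day score is available, leave its 6-week value out of the effectiveness and trajectory models. That leaves two follow-up points.

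Keep all days in the denominator in the main analysis. Readmission or detention can follow from substance use after randomisation, and legal involvement is itself an outcome, so excluding controlled-setting days belongs in a sensitivity analysis only.

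The cost is a few added or reworded items, some departure from the standard instrument, and follow-up scores off the usual 90-day metric. The change has to precede data collection, because a 90-day total cannot be split afterwards. If the full protocol already uses since-discharge recall, correcting Table 3 is enough.

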### Retention procedures

Multiple steps will be taken to prevent attrition from the study follow-up assessments. First, during the baseline assessment, multiple sources of contact information will be recorded for parents and adolescents. In addition to extensive personal contact information, parents will provide detailed contact information of two friends or family members (“locators”) who can be contacted if research staff is unable to reach them. Follow-up reminders will be made via phone, text, and/or mail, depending on the parents’ preferences. The research team will meet weekly to review no-shows and outreach attempts, and discuss plans to connect with missing participants. Parents and adolescents will each receive an escalating schedule of compensation in the form of gift cards for completing the baseline ($40) and three follow-up assessments ($50, $50, $60, respectively).

### Data analysis plan

All 60 parents will be included in statistical analyses consistent with an intent-to-treat (ITT) model. Prior to the main analyses, descriptive statistics will be run on key variables to examine distributional properties, identify outliers, and transform variables as needed. The two treatment conditions will be compared on baseline demographic and clinical variables using basic two-group independent sample t-tests. Using a *p* < .05 criterion, significant pre-existing baseline differences between conditions on any variables will be controlled in subsequent analyses.

GAIN-Q3 data will be entered into the GAIN’s proprietary software, which offers instant error checks and validation reports to prevent missing data. Other forms will be entered directly into study laptops using REDCap (Research Electronic Data Capture), a secure web-based application, to reduce missing data and entry errors. Attrition analyses will compare follow-up completers and non-completers on baseline clinical and demographic variables to determine if they differ systematically. If no systematic differences are found between completers and non-completers, then missing data will be estimated using multiple imputation methods with five datasets, an approach that has been shown to generate unbiased estimates when data are missing at random or missing completely at random [93].

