### Study enrollment and randomization

In accordance with institutional review board procedures at Brown University and Rhode Island Hospital, parents of all newly admitted adolescents will receive a Consent to Contact (CoC) form as part of the standard intake process at the residential center. Parents that sign a CoC form will then be contacted by research staff in one of two ways. If the adolescent is admitted Monday through Friday during normal business hours (which accounts for about 80% of new intakes), research staff located on site will immediately approach the parents and invite them to initiate the consent process. If the adolescent is admitted after hours or on weekends, research staff will contact the parents using the preferred contact information provided.

Parents will provide written informed consent and adolescents will provide written assent in separate private rooms at the residential center. If an adolescent chooses not to participate, the parent will be given general feedback that the family did not qualify so as to protect the adolescent’s privacy. Parents and adolescents may choose to conduct the informed consent process and all other study procedures in English or Spanish.

Parents will be given the choice whether to return for the baseline assessment or complete it immediately following informed consent. In the Phase 2 trial, randomization will occur within 24 h after the baseline assessment. Parent-adolescent dyads will be randomized to either SC or PW+ using urn randomization balanced on sex, severity of substance use, and preferred language (English vs. Spanish). Randomization will be conducted by a Co-Investigator, not involved with the assessment process, as soon as a parent consents to participate. Condition assignments will be placed in sealed envelopes and given to the independent evaluator. The evaluator will give parents their sealed envelope indicating that their treatment condition immediately after completion of the baseline assessment. If the parent is assigned to PW+, the evaluator will schedule the first in-person coaching session.

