#### Secondary outcomes: adolescent variables

Secondary outcomes include adolescent substance use and associated high risk behaviors (i.e., sexual risk-behavior, truancy, and criminal involvement). Analyses will compare trajectories of use over the post-discharge period, controlling for baseline status as a covariate. For each dependent variable, separate repeated measures Analysis of Covariance will test the influence of condition, controlling for the following covariates: baseline status on the dependent variable, baseline differences between groups, and any mental health or substance use treatment received over the follow-up period. The effect of PW dosage on each dependent variable will be calculated and partial eta squared (η2) will be used to estimate the proportion of variance caused by PW. The primary analytical goal will be to provide measures of association and 95% confidence intervals to reveal the effect size of PW on each dependent variable.

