#### Putative mediators: parental communication and monitoring

The study will be underpowered to test mediation, but will examine the effects of PW on putative mediators. A repeated measures Analysis of Covariance will whether assignment to the PW+ condition has a significant effect on either of the putative mediators, controlling for any treatment received. In addition, we will calculate change in the putative mediators over each time interval as well as change in the dependent variables over each time interval. Correlations between change in the putative mediators and change in the dependent variables will be examined; significant positive correlations greater than *r* = .20 will be flagged as worthy of further analysis in a future trial. The goal of these analyses is to find promising trends to pursue in a larger fully powered trial.

For both the secondary outcome analyses and the mediator analyses, the investigators will also attempt to fit latent growth models to the data. Latent growth models represent a flexible approach to analyzing change that enable a comparison of conditions at each time point while accounting for the correlation of observations over time [94]. Although convergence is challenged in a small sample, latent growth models have been fit to samples as small as *n* = 22 [95, 96]. The study PI has conducted multiple analyses using latent growth models [32, 97, 98] and will lead the longitudinal analyses.

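### Covariates are chosen by baseline tests at p < .05, while the three factors used to balance randomisation are named in no model

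*Protocol article*

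**What the plan says.** The Data analysis plan compares the two arms on "baseline demographic and clinical variables using basic two-group independent sample t-tests". It then sets the consequence: "Using a *p* < .05 criterion", "significant pre-existing baseline differences between conditions on any variables will be controlled in subsequent analyses".

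The section on secondary outcomes carries this into each repeated measures ANCOVA. Its covariates are "baseline status on the dependent variable, baseline differences between groups, and any mental health or substance use treatment received over the follow-up period". The section on putative mediators asks whether assignment to PW+ "has a significant effect on either of the putative mediators, controlling for any treatment received"; it names no other covariate.

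Allocation, described under Study enrollment and randomization, uses "urn randomization balanced on sex, severity of substance use, and preferred language (English vs. Spanish". None of these three factors is listed as a covariate in either model. Each could enter only by failing a baseline test.

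The purpose of the secondary analyses is estimation: "The primary analytical goal will be to provide measures of association and 95% confidence intervals". The sample size section expects about 50 complete dyads out of 60. It will use the observed effect, together with feasibility and acceptability, to judge whether a larger trial is warranted and how large it should be.

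**The concern.** Dyads are randomised, so with sound allocation a significant baseline difference is a chance event. A test of that difference selects variables by how unbalanced they happen to be, not by whether they predict the outcome. Three things follow.

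- The adjustment set cannot be known until the baseline data are seen, and it may include variables that do nothing but use up degrees of freedom and correlate with arm.
- A prognostic variable with a moderate imbalance that falls short of significance is left out.
- The rule works against the design. The urn makes its own factors unlikely to differ significantly, so the variables thought important enough to balance are the least likely to be adjusted for.

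The stake is the precision of effect estimates and intervals in a sample of about 50, which feed the decision on a larger trial. T-tests are also an awkward tool for categorical baseline variables, but that falls away if the tests are dropped.

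**Working it through.** **Inputs from the article.** 60 randomised; 15–20% loss, so 60 × 0.80 = 48 to 60 × 0.85 = 51, consistent with the stated 50; threshold p < .05; three urn factors. **Assumed, because not stated:** two-sided tests, 1:1 allocation, and the number of baseline variables tested.

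**The plan's own figures.** n per group = 2(1.960 + 0.842)² / d². For d = .3 this gives 175, and for d = .5 it gives 63; the t-based solution gives 176 and 64. The stated 175 and 64 are reproduced, and this point does not change them.

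**Chance of at least one flag.** For k independent tests, 1 − 0.95^k:

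| k (assumed) | P(at least one flagged) |
|---|---|
| 5 | 23% |
| 10 | 40% |
| 15 | 54% |
| 20 | 64% |

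Correlated baseline scales would change these figures.

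**What the rule does not catch.** For an observed standardised difference d at 30 v 30, t = d × √(30/2) = d × 3.873. With d = 0.4, t = 1.55 on 58 df, p about .13: not adjusted for. Significance needs t of about 2.00, that is d above 2.00 / 3.873, about 0.52.

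**Effect on precision.** A simulation of about 3,000 trials per scenario used N = 50, urn-type allocation on three binary factors, ten further independent baseline variables, a baseline–outcome correlation of .5 and a single follow-up value. It compared ANCOVA under the p < .05 rule with ANCOVA using the three urn factors prespecified. Both included the outcome's baseline value. The share of residual variance explained by the urn factors is not in the article, so it is varied.

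| Residual variance explained (assumed) | Mean SE, p < .05 rule | Mean SE, urn factors fixed | Ratio | Power at d = .5, rule → fixed |
|---|---|---|---|---|
| 0% | 0.255 | 0.252 | 1.01 | .48 → .49 |
| 10% | 0.255 | 0.239 | 1.07 | .47 → .51 |
| 20% | 0.255 | 0.225 | 1.13 | .47 → .57 |
| 30% | 0.255 | 0.210 | 1.22 | .49 → .64 |

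- Some variable was flagged in 41–42% of trials; an urn factor was flagged in under 2%.
- Against a model with the baseline outcome alone, the rule itself raised the SE from 0.247 to 0.255, about 3%.
- Type I error under the rule was .048, .053, .041 and .039 down the table. Monte Carlo error is about √(.05 × .95 / 3000) = .004, so the last two are below .05 and none is convincingly above it.
- Part of the 13–22% is a reported SE that overstates the true spread. The empirical SD of the estimate fell from 0.246 to 0.225 (ratio 1.09) at 20% and from 0.246 to 0.218 (ratio 1.13) at 30%.

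**The case against.** The best defence is that the damage is small and falls on secondary material. Much of that stands.

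- **Baseline outcome status is already fixed.** It is in every secondary-outcome model whatever the tests show. For the substance-use outcomes it carries most of the information in severity, so the omission there concerns mainly sex and language. For sexual risk, truancy, criminal involvement and the mediators, severity is also left out.
- **The factors are not shown to be prognostic.** A reader might infer that a known predictor is being omitted. The article gives no evidence that sex, language or severity predicts these outcomes, so any precision loss must be given as a range that starts near 1%.
- **The intervals are not invalid.** A reader might infer that the 95% intervals are wrong or the tests too liberal. The calculations show no inflation. At most the intervals are somewhat too wide, with type I error about .04 when the factors are assumed to explain 20–30% of residual variance.
- **A power figure does not apply.** It is tempting to say that a severity difference of d = 0.4 would be detected only about a third of the time. That is power against a population difference, which randomisation sets to zero, and severity is a variable the urn tends to balance. The valid statement concerns an observed imbalance in some other prognostic variable.
- **Balance is not guaranteed.** The urn is probabilistic, so its factors are unlikely, not unable, to be flagged.

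The defence that an unseen analysis plan may settle the covariates does not stand. The article itself fixes a selection rule and a covariate list.

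**Conclusion.** The point holds in a limited form. The article commits to choosing covariates by baseline significance and names none of its randomisation factors in the secondary-outcome or mediator models. The adjustment set is thus data-dependent, which is a fault whether or not the factors are prognostic. The added cost in standard error runs from about 1% to roughly 13–22%, depending on an assumption of 0% or 20–30% of residual variance explained; the simulation's simplifications (independent extra variables, one follow-up) also apply.

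It should not be read as threatening the trial's main conclusions. Feasibility and acceptability are judged against percentage targets without a covariate model. The change is worth making because it is cheap and improves the estimates meant to inform a larger trial.

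**What to change.** 1. Delete the p < .05 rule from the Data analysis plan, and remove the entry for baseline group differences from the secondary-outcome covariate list.
2. In every secondary-outcome and mediator model, prespecify the baseline value of that outcome or mediator, plus sex, language and severity, each coded as it was for the urn.
3. Present baseline characteristics by arm descriptively, without tests.

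No new data are needed, since the three factors must be known in order to randomise, and no stated sample size changes. The cost is wording and about three degrees of freedom if each factor is binary, more if severity has further levels.

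Language may be sparse. About 20% of admissions are Hispanic, so even if all those families preferred Spanish (assumed; the share is not given) that would be about 0.20 × 50 = 10 dyads. State in advance, without reference to outcomes by arm, how a very small language category will be handled.

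Whether treatment received during follow-up belongs in these models is a separate question that this change does not settle.
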